# The TEMP-PREVENT trial: a study protocol for a randomized, double-blind, placebo-controlled clinical trial of etidronate for treatment in young adult patients with pseudoxanthoma elasticum

**DOI:** 10.1186/s13063-025-09064-6

**Published:** 2025-10-23

**Keywords:** Pseudoxanthoma elasticum, Etidronate, Randomized controlled trial, Arterial calcifications

## Abstract

**Background:**

Pseudoxanthoma elasticum (PXE) is a genetic disease with autosomal recessive inheritance, characterized by slowly progressive ectopic calcification in the elastic fibers of the skin, Bruch’s membrane in the retina, and in the arteries. Etidronate was found to be effective in halting the progression of arterial calcification in an earlier trial, including middle-aged patients with PXE with manifest arterial disease. It is uncertain if there are similar effects in young adult patients with PXE.

**Methods:**

The TEMP-PREVENT study is a randomized, double-blind, placebo-controlled clinical trial, investigating the effect of 20 mg/kg cyclical etidronate on ectopic calcification in PXE patients of ≥ 18 and ≤ 55 years. The study is conducted at the University Medical Center, Utrecht, the Netherlands. The primary endpoint is the change in arterial calcification volume between baseline and 24 months in the leg arteries and carotid siphons, as measured on low-dose unenhanced Computed Tomography. Secondary endpoints are changes in dermatological, ophthalmological, vascular, laboratory, cognitive and quality of life outcomes/parameters. Recruiting started in April 2023. Results are expected in 2027 and will be dispersed through peer-reviewed journals and international conferences.

**Discussion:**

PXE is a rare genetic disease for which there is currently no registered treatment. The TEMP-PREVENT trial is set out to evaluate the effects of etidronate in young adult patients with PXE.

**Trial registration:**

The trial is registered at the Dutch Central Committee on Research Involving Human Subjects (CCMO) (registration number: NL75350.041.21), European Union Clinical Trials Register (EudraCT number: 2021–000434-34), and at ClinicalTrials.gov (ID: NCT05832580, registration date 2023-04-14).

## Introduction

### Background and rationale

Pseudoxanthoma elasticum (PXE) is an autosomal recessive genetic disorder characterized by slowly progressive ectopic calcification in the elastic fibers of the skin, Bruch’s membrane in the retina, and the arteries. The exact prevalence is unknown, but is estimated to be 1 in 25,000–50,000 [1–4]. Clinical manifestations cause considerable morbidity, with ocular events leading to legal blindness, skin lesions developing in early infancy, and vascular complications resulting in peripheral artery disease, gastric bleeding, and increased occurrence of cerebrovascular events [5–7]. Currently, there is no registered treatment for PXE. 

PXE is caused by pathogenic variants in the *ABCC6* gene [8]. The exact role of the *ABCC6* transporter is not fully elucidated, but the generally accepted hypothesis is that the *ABCC6* protein acts as an ATP transmembrane transporter in the liver and kidneys [9]. Because ATP is metabolized to ADP and inorganic pyrophosphate (PPi), the absence of functional *ABCC6* in PXE leads to reduced plasma concentrations of PPi, a potent calcification inhibitor [10–13].

Bisphosphonates are chemically stable analogues of PPi [13]. Bisphosphonates have been widely used for over 40 years to treat conditions such as osteoporosis and have proven to be remarkably safe ^14,15^. The molecular structure of the different bisphosphonates results in either a strong osteoclast-inhibiting potential or more affinity to bind to hydroxyapatite [14, 15]. This makes etidronate particularly interesting in the treatment of PXE, because it has a relatively low impact on osteoclast activity, and a large impact on inhibition of mineralization [16].

A proof-of-concept study demonstrated that etidronate reduced soft tissue calcification in an *ABCC6* -/- mice model [17]. This finding was confirmed in a randomized, double-blind, placebo-controlled clinical trial in PXE patients [18]. After 1 year of treatment, arterial calcification had decreased by 4% (IQR, − 11% to 7%) in the etidronate group and increased 8% (IQR, − 1% to 20%) in the placebo group [18, 19]. Arterial calcification was, however, not a primary endpoint. Moreover, the trial included only PXE patients with extensive arterial calcification, resulting in a relatively older and more affected population. It is unclear if arterial calcification is equally inhibited in a young adult population with fewer PXE manifestations. Moreover, etidronate only inhibits the growth of calcification and does not reverse it, so prevention of further ectopic calcification early on may be even more beneficial than inhibiting it at a late stage. Another benefit of a young trial population is that calcification of Bruch’s membrane is better visible in eyes that show no gross structural damage to the macula, such as choroidal neovascularization or pigment epithelium or retinal atrophy, as often happens in later stages of PXE.

Therefore, in the TEMP-PREVENT trial, we aim to determine the effect of etidronate treatment in PXE patients with minimal or no existing arterial calcification on the development and progression of arterial calcification, and also on ocular calcification in Bruch’s membrane, dermatological calcifications, and cardiovascular outcomes.

### Trial design

The TEMP-PREVENT trial (an acronym for “Treatment of Ectopic Mineralization in Pseudoxanthoma elasticum-PREVENTion”) is a randomized, double-blind, placebo-controlled clinical trial comparing the effects of 24 months of treatment with etidronate versus placebo in patients with PXE aged 18 to 55.

## Methods

### Study setting

The study will take place at the UMC Utrecht Expertise Center for Pseudoxanthoma elasticum (UECP) in Utrecht, the Netherlands. This is the Dutch National Expertise Center, in which most Dutch patients with PXE are seen. Patient recruitment started in April 2023. This study has received funding from the Dioraphte Foundation, the Dutch PXE Foundation (Stichting PXE-Fonds), the Dutch Eye Foundation (de Oogvereniging), and the Dutch Eye Society (het Oogfonds). The trial is registered at the Dutch Central Committee on Research Involving Human Subjects (CCMO) (registration number: NL75350.041.21), European Union Clinical Trials Register (EudraCT number: 2021–000434-34), and at ClinicalTrials.gov (ID: NCT05832580). This protocol was developed in accordance with the SPIRIT reporting guidelines.

### Study population

Patients will be recruited from the UECP located in the University Medical Center Utrecht (UMCU) and by recruitment through (social) media, for example, using the UMCU website, the Dutch PXE Society, newsletters, yearly patient days, and conferences. In total, 76 patients will be recruited. To be eligible to participate in this study, a subject must meet the following inclusion criteria: (1) age between 18 and 55 years, (2) definitive or probable diagnosis of PXE according to the Plomp criteria [20], and (3) fertile women should take adequate contraceptive measures. Reasons for exclusion are the following: (1) patients unable or unwilling to sign for informed consent, (2) for women: pregnant, lactating, or fertile and wish to become pregnant within 3 years, (3) estimated glomerular filtration rate below 30 ml/min/1.73m^2^ according to the CKD-EPI equation [21], (4) known abnormality of the esophagus that would interfere with passage of the drug (e.g., esophagus stenosis), (5) chronic diarrhea (> 1/month), (6) known osteomalacia, (7) hypocalcemia (calcium < 2.20 mmol/L corrected for albumin), (8) vitamin D deficiency (< 35 nmol/L), (9) use of bisphosphonate in the last 5 years, (10) known sensitivity to etidronate, (11) any other medical or social condition that, at the discretion of the Principal Investigator, might put the subject at risk of harm during the study or might adversely affect the interpretation of the study data. The eligibility screening will be performed by the treating physician. Individuals withdrawn from the study (for any reason) will be replaced.

### Informed consent

All patients who fit the criteria for inclusion will be contacted by phone by their treating physician. During this call, study procedures will be briefly explained to the subject, and if the patient is interested in participation, an envelope with the patient’s information folder (PIF), including an informed consent form, will be sent to the subject. After the patient has received and read the contents of this envelope, the patient will again be called and, if still interested, invited for a screening appointment. There will be at least 10 days between sending the PIF and this second call to allow potential participants enough time to consider their decision. During the screening appointment in the UMCU, the patient’s understanding of the study and its procedures will be verified, and an informed consent form will be signed before any procedures by the patients and research physician. The informed consent procedure will be executed by a trained research nurse or physician.

### Intervention

Patients will be randomly assigned to either daily, oral etidronate capsules of 200 mg or 400 mg at 20 mg/kg for 2 weeks, followed by 10 weeks off (9 cycles in total), *or* an identical product without the active pharmacological substance (i.e., a placebo) in the same cyclical regimen, for a total of 24 months. The choice of a placebo control group was made with careful consideration and is made because no proven effective treatment exists for PXE.

Etidronate capsules are administered orally, as oral intake is the safest, convenient, and cost-effective mode of administration. Etidronate is best absorbed on an empty stomach. Patients will be thoroughly explained how to ingest the product: on an empty stomach, in an upright position, and are instructed to remain in an upright position for 30 min. Subjects are advised to refrain from simultaneous intake of calcium-containing products to improve absorption. The total dose per patient is calculated based on their body weight and then rounded to the nearest dose divisible by 400 mg.

At the initial product dispensing and each follow-up visit, an adherence reminder session will take place. At follow-up visits, patients will be asked about any problems they have with taking their study medication. Also, any reasons for missed doses will be addressed. Moreover, patients will have the opportunity to ask questions, and the importance of following our study guidelines will be emphasized. Patients can continue to take medications for other conditions as normal. The sponsor/investigator has liability insurance, which is in accordance with Article 7 of the WMO. The sponsor also has insurance, which is in accordance with the legal requirements in the Netherlands (Article 7 WMO). This insurance provides cover for damage to research subjects through injury or death caused by the study.

There is already forty years of experience with etidronate, and the side-effect profile is well-known and relatively mild. The most common side effects are gastrointestinal complaints, including loose stools, abdominal discomfort, and nausea [22]. A rare, but serious adverse effect of bisphosphonates is osteonecrosis of the jaw. This is, however, only reported in patients with intravenous bisphosphonate use, mostly when treating cancer-related hypercalcemia ^22^. Theoretically, etidronate could have an effect on calcium homeostasis and bone turnover. Therefore, measurements of plasma calcium, phosphate, and vitamin D will be included as safety measures [23].

Etidronate and the matching placebo will be produced by Pharmacy A15, Gorinchem, the Netherlands. The products will be packaged and shipped to the Department of Clinical Pharmacy of the UMCU. At every follow-up visit, participants will be asked to take any redundant product and the empty packaging material to monitor drug adherence.

## Outcome measures

The primary endpoint in the TEMP-PREVENT trial is the percentage change in arterial calcification volume in the carotid siphons and leg arteries, measured on low-dose (< 3 ms for a 70 kg adult), unenhanced, thinslice, multi-detector CT scan (CT7500, Philips Healthcare, Cleveland, Ohio). Tube voltage (kVp) is set at 120, and tube current (mAs) varies between patients, reliant on body weight. Arterial calcification volume in microliter (µL) will be measured at a threshold of 130 Hounsfield Units using commercially available software (Calcium Scoring Heartbeat, Philips Advanced Visualization Workspace, Philips Healthcare).

Secondary endpoints are changes in dermatological, ophthalmological, vascular, laboratory, cognitive, and quality of life parameters. *Dermatological* outcomes are changes in elastin degradation and calcification in skin biopsies. A 3-mm punch biopsy will be taken from non-lesional skin, at least 2 cm from a pseudoxanthoma lesion, on the back of the neck just below the hairline, and under local anaesthesia. To ensure standardization and repeatability, a photograph of the biopsy site will be taken, and at the 24-month follow-up (M24), a second biopsy will be performed at least 2 cm from the original site to avoid scar tissue interference. The extent of elastin degradation will be scored on Verhoeff-Van Gieson stains, and the extent of calcification will be scored on Von Kossa stains [24]. All analyses will be performed by an experienced dermatopathologist. *Ophthalmological* outcomes are changes in best-corrected visual acuity and low luminance visual acuity, contrast sensitivity, changes in the infrared images, autofluorescence patterns, and the appearance of new choroidal neovascularisations on optical coherence tomography (OCT)-angiography, Bruch’s membrane reflectivity on high-definition spectral domain OCT, and the number of anti-VEGF injections. OCT is a non-invasive imaging technique requiring mydriatic eyedrops [25]. *Vascular* outcomes are changes in carotid intima-media thickness (cIMT) by ultrasound, which is a non-invasive measurement to establish the carotid atherosclerotic vascular disease and measures the thickness of the tunica intima and media of the carotid artery [26]. Moreover, changes in pulse wave velocity [27] and pulse wave analysis [28] are measured to reflect changes in arterial stiffness. Ankle-brachial index [29], the six-minute walking test [30], and the WELCH questionnaire [31, 32] are compared between baseline and 24 months of follow-up to reflect peripheral arterial disease. Moreover, changes in the pulsatility index of the intracranial carotid arteries and middle cerebral arteries by 7T-MRI are compared. The incidence of major adverse cardiovascular events (TIA, stroke, myocardial infarction, and/or cardiovascular death) is counted to see if etidronate lowers the risk of these events. *Laboratory* outcomes are changes in calcium, phosphate, ASAT, ALAT, eGFR, desmosin, and inorganic pyrophosphate [33]. *Cognitive outcomes* are changes in memory, attention, and executive function. Memory will be assessed with the Rey auditory verbal learning test with immediate recall, delayed recall, and recognition [34]. Attention will be tested with the Trail Making Test-A [35], Stroop Test reading and colour naming [36], and Digit Span Forwards WAIS-III [37]. Executive function will be tested with the Trail Making Test-B [35], Stroop Test colour-word Interference [36], Digit Span Backwards WAIS-III [37], Semantic fluency [38], and the Brixton Test [39]. Composite Z-scores will be calculated for the different cognitive domains using normative data from the Advanced Diagnostics Infrastructure (ANDI) [40]. The differences in change in cognitive functioning between baseline and follow-up will be compared between the intervention group and the control gro*up. Quality of life* outcomes are changes in EQ-5D [41], PROMIS 10 [42], PROMIS PF [43], and USER P [44].

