## Statistical analysis

Descriptive data will be presented as numbers and percentages for categorical data, mean and standard deviations for normally distributed continuous data, or median and interquartile ranges for non-normally distributed continuous data. Data will be analyzed applying the intention-to-treat principle. When missing data occurs, potential patterns will be analyzed and appropriate methods used accordingly (i.e., complete case analyses or multiple imputation) [44]. Researchers will be blinded during statistical analysis. The mean change (delta) from baseline to 24 months will be calculated for both groups for all primary and secondary endpoints. These deltas will be analyzed with a two-tailed Student’s *t*-test or Mann–Whitney *U* test as appropriate. In the case of relevant baseline differences, adjustments will be made with regression models. Both adjusted and unadjusted models will be presented. Also, if the numbers are sufficient, subgroup analyses will be performed in patients with different PXE phenotypes (predominantly ophthalmological phenotype, predominantly dermatological phenotype, predominantly vascular phenotype).

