## Discussion

The TEMP-PREVENT trial will provide insight into the effect of 24 months of treatment with etidronate in young adult patients with PXE.

Previously, the TEMP-trial has shown that a year of etidronate treatment in PXE patients gave a reduction in arterial calcification of 4% (interquartile range [IQR], − 11% to 7%) when compared to placebo. This trial did, however, exclusively enroll patients with measurable arterial calcification, comprising, therefore a relatively older and more profoundly affected study population. It remains uncertain to what extent arterial calcification can be halted in a young adult population. 

A young adult study population has the additional advantage that the retina is not yet, or at least to a lesser degree, affected by choroidal neovascularization and atrophy [45]. The TEMP trial showed a difference in neovascularizations between the etidronate (1) and placebo group (9); however, post hoc analysis showed this was likely not an effect of etidronate but could be explained by the unequal distribution of patients more at risk of CNV activity among the two groups [46]. Using newly developed techniques in measuring reflectivity of Bruch’s membrane in patients without extensive structural damage of the macula, the aim is to better study the effect of etidronate on ophthalmologic manifestations in PXE patients.

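### The primary endpoint is a percentage change from baseline, which has no value at zero calcification, yet the trial's aim covers patients with no calcification and entry sets no minimum volume

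*Protocol article*

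**What the plan says.** Outcome measures defines the endpoint as a ratio to baseline: "The primary endpoint in the TEMP-PREVENT trial is the percentage change in arterial calcification volume in the carotid siphons and leg arteries". The same section says how volume is obtained: "Arterial calcification volume in microliter (µL) will be measured at a threshold of 130 Hounsfield Units". A scan with no voxel at or above that threshold therefore has a volume of 0 µL.

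Background and rationale gives the aim: "we aim to determine the effect of etidronate treatment in PXE patients with minimal or no existing arterial calcification on the development and progression". Study population admits patients on "1) age between 18 and 55 years, (2) definitive or probable diagnosis of PXE according to the Plomp criteria", plus contraception for fertile women. Neither the inclusion nor the exclusion criteria set a minimum or maximum calcification volume.

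Other sections word the scale differently. The Abstract has "The primary endpoint is the change in arterial calcification volume between baseline and 24 months in the leg arteries and carotid siphons", with no mention of percentage. Statistical analysis computes a mean change from baseline to 24 months for every endpoint and continues: "These deltas will be analyzed with a two-tailed Student’s *t*-test or Mann–Whitney *U* test as appropriate". It also commits to intention-to-treat. The Sample size calculation works with a relative difference of 10% over 2 years, scaled down from the earlier trial. Of that trial the Discussion says: "This trial did, however, exclusively enroll patients with measurable arterial calcification". The article gives no rule for a zero baseline.

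**The concern.** A percentage change divides by the baseline value. In the earlier trial every patient had measurable calcification, so the ratio always existed. This trial removes that entry condition on purpose and keeps the ratio.

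Two consequences follow. A patient with 0 µL at baseline has no endpoint value, whether or not calcification appears by 24 months, although new calcification is something the aim asks about. A patient with a few microlitres at baseline can score several hundred percent on a small absolute change, and a comparison of means gives that value full weight.

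At stake are who is counted in the primary analysis, how much power is left, and whether the scale is settled before the treatment code is opened. Choosing an absolute, relative or transformed scale after unblinding would look data-driven.

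**Working it through.** **1. The plan's own figure.** No SD is stated. Background and rationale gives 1-year interquartile ranges for the earlier trial: −11% to 7% on etidronate (width 18) and −1% to 20% on placebo (width 21). Assuming normality, SD = width / 1.349:

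- etidronate 18 / 1.349 = 13.3; placebo 21 / 1.349 = 15.6
- pooled SD = √[(13.3² + 15.6²) / 2] ≈ 14.5 points
- n per arm = 2 × [14.5 × (1.960 + 0.842) / 10]² ≈ 33.0

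This reproduces the stated 33 per arm (34 if the t distribution is used). So 33 per arm matches the spread of percentage changes in patients who all had measurable calcification.

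**2. Zero baseline.** Endpoint = 100 × (V24 − V0) / V0. With V0 = 0 and V24 = 0 this is 0/0. With V0 = 0 and V24 > 0 it is a division by zero. Neither result can enter a mean or be given a proper rank. Multiple imputation, one of the plan's options for missing data, cannot supply a quantity that is undefined.

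**3. Power if zero-baseline patients are lost.** The share is not in the documents, so a range is assumed. With 38 per arm and 15% dropout, 38 × 0.85 = 32.3 remain. A two-sample t-test at 5% two-sided is used. The standardised effect of 0.70 is the one at which 33 per arm gives 80% power by t-test (SD about 14.3).

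| Zero share (assumed) | Evaluable per arm | Power |
|---|---|---|
| 0% | 32.3 | 79% |
| 10% | 29.1 | 75% |
| 20% | 25.8 | 69% |
| 30% | 22.6 | 63% |

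Starting from 33 per arm with SD 14.5 gives 79%, 74%, 69% and 63%, so the result does not hinge on that choice.

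**4. Near-zero baseline and means.** One patient at +330% contributes 330 / 33 = 10 points to an arm mean. As an example, 5 to 30 µL is +500%. In an arm otherwise averaging +8%, it moves the mean by (500 − 8) / 33 = 14.9 points and raises the arm SD from 14.5 to about 87.

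**5. The two tests the plan allows.** Simulation with 33 per arm and a true difference of 10 points in the other patients. Near-zero patients are assumed to have baselines of 2–20 µL and mean absolute changes of 10 µL (placebo) and 5 µL (etidronate), SD 10 µL.

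| Near-zero share (assumed) | t-test power | Mann–Whitney power |
|---|---|---|
| 0% | 78% | 76% |
| 5% | 40% | 72% |
| 10% | 27% | 68% |
| 20% | 19% | 59% |

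The distortion falls mainly on the t-test. The rank test loses much less, but it does nothing for undefined values.

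**The case against.** The strongest reply has four parts.

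- **The rank test is already in the plan.** Extreme percentages are the situation in which Mann–Whitney would be judged appropriate. This stands. A reader might infer that a few tiny denominators must decide the result; that is true of means only, and the plan does not commit to means.
- **The extent is unknown.** Eligibility goes by age (18 to 55) and diagnosis, with no upper limit on calcification, so heavily calcified patients can enter. If the territories are summed, a zero total needs both siphons and legs to be clear. This also stands, so the figures above are ranges and not forecasts.
- **The analysis plan may hold a zero rule, and a plain change in µL exists at zero.** This stands in part. An offset or handling rule is commonly left to the analysis plan, and its absence is not the point here. The point is that the article fixes the endpoint on a scale that conflicts with its own aim and entry criteria, while the Abstract and Statistical analysis word the scale differently. It would go too far to say that the question on new calcification will certainly go unanswered.
- **No single replacement is clearly better.** This stands. A reader might infer that a transformed-scale ANCOVA is needed to rescue power, but the documents give no baseline distribution to support that. A simulation assumed 32 per arm, 20% zeros, scan error of 8 µL plus 5%, growth of 16% versus 6% (SD 10%), new onset of 10 versus 5 µL on average and log-SD 1.0 to 1.5. Mann–Whitney on percentage change with zeros dropped came close to square-root ANCOVA on all patients: 0.30–0.36 versus 0.34–0.36 at a median baseline of 100 µL, 0.55–0.59 versus 0.51–0.54 at 300 µL, and 0.71–0.73 versus 0.63–0.68 at 1000 µL. The case for change is that the endpoint must exist for every patient, not that one model wins on power.

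**Conclusion.** The concern holds in this form: as defined under Outcome measures, the primary endpoint has no value for a patient with zero baseline volume, and the trial's aim and eligibility let such patients in. That part is arithmetic and needs no assumption. Applied as written, the definition leaves these patients unscored and outside the primary analysis, which conflicts with the intention-to-treat commitment.

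The size is conditional. Power falls from about 79% to 75%, 69% or 63% if 10%, 20% or 30% have zero baseline, taking the planned 10-point difference and the spread implied by the earlier, more calcified population. Near-zero baselines can seriously distort a t-test and affect Mann–Whitney far less. Confidence is high on the definition and moderate on the impact. Because the defect lies in the primary endpoint and can still be repaired without new data, it should be corrected.

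**What to change.** Before unblinding, and by formal amendment as Ethical considerations requires:

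- Define one primary endpoint on a scale that exists at zero: total siphon plus leg volume at 24 months, adjusted for baseline volume. An ANCOVA on a transformed scale that admits zeros, or a rank-based analysis, would serve. Name one as primary.
- Include all randomised patients under the intention-to-treat principle, whatever their baseline volume.
- Keep percentage change as a supportive summary in patients above a measurable baseline volume set in advance.
- Use the same definition in the Abstract, Outcome measures and Statistical analysis. State in the Sample size calculation that the 33 per arm was derived for a 10% relative difference, so that readers see it was not derived on the new scale.

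The cost is an amendment with ethics approval and revised text. Recruitment closed in December 2024 and the last visit is scheduled for December 2026; no extra scans or patients are needed. Two downsides: results compare less directly with the earlier trial's percentages, and power may be somewhat lower if most baselines turn out to be large.

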
## Participant timeline

Abbreviations: *CT* computed tomography, *VA* visual acuity, *CS* contrast sensitivity, *IR* infrared, *FAF* fundus autofluorecence, *OCTA* optical coherence tomography angiography, *SD-OCT* spectral domain optical coherence tomography, *anti-VGEF* anit vascular endothelial growth factor, *MRI* magnetic resonance imaging, *cIMT* carotid Intima media thickness, *PWV* pulse wave velocity, *ABI* ankle brachial index, *ASAT* aspartate aminotransferase, *ALAT* alanine aminotransferase (Table 1).

**Table 1 Tab1:** Schedule of study procedures and visits

Time:		M0	M6	M12	M18	M24
Visit:	1 (screening)	1		2		3
Eligibility screening	X					
Informed consent	X					
Low dose CT of legs and head (siphons)		X				X
Dermatological measurements						
Skin biopsy		X				X
Ophthalmological measurements						
Measurement of VA and CS		X				X
Fundus imaging (IR, FAF and OCTA)		X				X
SD-OCT scanning		X		X		X
No. of anti-VEGF injections		X	X	X	X	X
Vascular measurements						
Cerebral MRI		X				X
cIMT, PWV, PWA, and ABI		X				X
6 min walk test		X				X
WELCH questionnaire		X				X
Laboratory measurements						
Plasma Pyrophosphate		X				X
Desmosine		X				X
Laboratory measurements for safety monitoring (Calcium, 25-OH vitamin D, Creatinine, Phosphate, Magnesium, Albumin, ASAT, ALAT)	X			X		X
EQ-5D		X				X
PROMIS 10		X				X
PROMIS PF		X				X
USER P		X				X

*CT* computed tomography, *VA *visual acuity, *CS *contrast sensitivity, *IR* infrared, *FAF *fundus autofluorecence, *OCTA* optical coherence tomography angiography, *SD-OCT* spectral domain optical coherence tomography, *anti-VGEF* anit vascular endothelial growth factor, *MRI* Magnetic resonance imaging, *cIMT* carotid Intima media thickness, *PWV* pulse wave velocity, *ABI* ankle brachial index, *ASAT* aspartate aminotransferase, *ALAT* alanine aminotransferase

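### The ankle-brachial index is analysed as a signed change, so a leg artery that calcification makes incompressible would be scored as improvement

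*Protocol article*

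**What the plan says.** Under Outcome measures, the ABI is a secondary vascular endpoint, grouped with a walking test and a questionnaire: "Ankle-brachial index [29], the six-minute walking test [30], and the WELCH questionnaire [31, 32] are compared between baseline and 24 months of follow-up". The stated purpose of the three is to capture peripheral arterial disease. Arterial stiffness is assigned to other measures, namely pulse wave velocity and pulse wave analysis. Table 1 (Participant timeline) places "cIMT, PWV, PWA, and ABI" at M0 and M24.

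The Statistical analysis section has one rule for everything: "The mean change (delta) from baseline to 24 months will be calculated for both groups for all primary and secondary endpoints". It continues: "These deltas will be analyzed with a two-tailed" t-test or a Mann–Whitney test, as appropriate. The only modification offered is this: "In the case of relevant baseline differences, adjustments will be made with regression models". The article states no direction of benefit for the ABI, no upper limit, and no handling of a falsely high value.

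The primary endpoint is the "percentage change in arterial calcification volume in the carotid siphons and leg arteries". The aim, under Background and rationale, concerns "PXE patients with minimal or no existing arterial calcification on the development and progression of arterial calcification".

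**The concern.** The ABI is a ratio of cuff-occlusion pressures, and it can become abnormal in two directions. A narrowed artery lowers the ankle pressure and the index. A stiff, calcified ankle artery needs more cuff pressure to close, which raises the index. A signed change treats every rise as good.

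In many trials this would be noise, similar in both arms. Here the treatment is directed at calcification in the same limb arteries, so the artefact itself may differ by arm. If etidronate slows calcification, newly incompressible legs would be expected more often on placebo, and each would enter the analysis as a large placebo improvement. A real benefit on the ABI could then be diluted, hidden or reversed. At stake is the reading of one secondary endpoint. The primary endpoint and the sample size are not touched.

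**Working it through.** The article gives no ABI figure to reproduce, so the size can only be illustrated.

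**Input from the article:** 33 evaluable patients per arm (Sample size calculation).

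**Assumed inputs, not in the article:** SD of the ABI change 0.10; a newly incompressible artery adds 0.40 to a patient's change; *k* such patients, all on placebo.

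**Shift in the arm difference** = *k* × 0.40 / 33
- *k* = 1: 0.40 / 33 = 0.012
- *k* = 3 (9% of the arm): 1.20 / 33 = 0.036

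**Standard error with no such patient** = 0.10 × √(2/33) = 0.0246

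**Standard error with three.** The placebo variance becomes 0.10² + (3/33)(30/33)(0.40²) = 0.0100 + 0.0132 = 0.0232. The standard error is √[(0.0100 + 0.0232)/33] = 0.0317.

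**Shift relative to the standard error that applies:** 0.0364 / 0.0317 = 1.15.

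**Difference detectable with 80% power** (2.8 × SE): 2.8 × 0.0246 = 0.069 without such patients, and 2.8 × 0.0317 = 0.089 with three.

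**Both planned tests, simulated on the same assumptions** (20,000 runs, no true effect on the other patients). The table shows how often etidronate appears significantly worse.

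| Affected placebo patients | t-test | Mann–Whitney |
|---|---|---|
| 0 | about 2.4% | about 2.4% |
| 1 | about 5% | about 4% |
| 3 | 14% | 8% |

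With three affected patients and a true ABI benefit of 0.07 in the rest, power is about 12% for the t-test and 43% for Mann–Whitney. The rank test limits the damage from extreme values, but it still ranks those patients as the most improved.

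**A graded version, also wholly assumed.** Suppose progression moves the ABI by 0.10 on placebo and by 0.05 on etidronate, and a share *f* of patients stiffen (rise) while the others narrow (fall). The expected difference, etidronate minus placebo, is (2*f* − 1)(0.05 − 0.10):
- *f* = 0: +0.05
- *f* = 0.5: 0
- *f* = 1: −0.05

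The same halving of progression can thus appear as benefit, no effect or harm. In this version the two tests reject at similar rates.

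**The case against.** The strongest reply is that the scenario may be rare. The trial aims at patients with little or no calcification, aged 18 to 55 and followed for 24 months, and the sample size section assumes a smaller effect than the earlier trial showed. Every ABI input above is assumed. The three-patient case also puts all the events in one arm, and a single case shifts the difference by only about half a standard error (0.012 / 0.0246). This stands as a limit on size. It does not exclude the problem, because the eligibility criteria under Study population set no calcification limit.

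A second reply is that the ABI is not read alone. CT measures leg calcification at the same visits, and the walking test, the questionnaire and the pulse wave measures are also available. A paradoxical rise could be noticed. That helps interpretation but does not correct the ABI comparison.

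A third is that a condensed article leaves such detail to the analysis plan. That would be fair if the article were silent. It instead fixes one rule for all secondary endpoints and names no exception.

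A reader might go further and infer that the sign of any ABI difference is uninterpretable, or that etidronate will look worse. The documents do not support either: they give no frequency of incompressible arteries, and the net direction in this population is unknown. Nor is the plan tied to a comparison of raw means, since Mann–Whitney is allowed and roughly halves the wrong-direction rate in the three-patient case. Finally, dividing 0.036 by 0.0246 gives about 1.5 standard errors, but that uses a standard error which the same three values have already inflated.

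**Conclusion.** The point holds in a limited form. Followed as written, the rule scores a newly incompressible leg as improvement in a trial whose treatment targets leg-artery calcification, and nothing else in the article corrects this. The direction of an ABI difference may therefore be ambiguous.

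The illustrated effect runs from negligible (no affected patient) to just over one standard error (three of 33, all on placebo). This rests on the assumed SD, jump and frequency, and on the general principle of cuff measurement, which the article does not discuss. It is a cheap improvement to one secondary endpoint and not a threat to the trial's main conclusion.

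**What to change.** Keep the change in ABI as the analysis, and pre-specify the following before unblinding:

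1. An upper limit (for example the conventional 1.40) above which a leg is classed as incompressible and abnormal.
2. A rank-based comparison of all randomised patients in which a newly incompressible leg ranks as worsened. The text should also say how two legs combine into one rank per patient, and how a leg already incompressible at baseline is ranked.
3. The number of low and of incompressible legs per arm at M0 and M24.
4. The mean change in legs compressible at both visits, as a sensitivity result only, because this selects on a post-randomisation value that treatment may affect.

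Replacing the change altogether by a comparison of categories is not needed, and it would lose sensitivity if few legs change class.

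The cost is analysis-plan wording, with no new measurement. The last visit is scheduled for December 2026 (Trial status); the same choice made after unblinding would be post hoc. The downsides are that a rank-based main result has a less direct effect size, and that the upper limit is a convention from outside the document.
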